### Qualitative Analysis

Content analysis using an inductive approach[61] will be used to identify categories and themes that occur in the transcribed text generated from the qualitative interviews[62]. Transcribed data will be entered into a database (ATLAS.ti) designed to capture and analyze qualitative data.

The text of ten interviews will be read independently by two investigators to gain an overall impression and to establish and define preliminary codes in response to the proposed questions[63,64]. After the initial analysis, the investigators will meet to reach a consensus on preliminary codes. These codes will be entered into a "code book," which will provide a detailed definition for each code[62]. Information related to methodological decisions and their rationale will also be documented[61]. Subsequent transcripts will be independently reviewed to identify and code text segments and to assess the inter-rater reliability of text coding. Kappa values of less than 0.8 will necessitate review of the coding structure.

Investigators will meet after each set of twenty interviews to revise the code book and add new codes as necessary, grouping them into thematic categories. The frequency of themes will be quantified and representative quotations will be identified[62,65]. The investigators will independently review the summarized information and verify it for consistency with the original text. Categorized information from the transcribed interviews will be entered in matrices to organize and display categories by treatment groups as a means of illustrating relationships among categories[66]. This information will then be summarized and interpreted. Findings will be discussed until consensus is reached. The frequency of themes will be quantified and representative quotations will be identified[62,65]. The frequency of responses in the thematic categories will be cross-tabulated with treatment group assignment and compared for between-group differences using Chi-square analysis. 95% confidence intervals will be calculated for these differences.

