### Qualitative measures

Qualitative interviews are conducted with patients individually at the end of the 12-week treatment period[52]. A schedule of questions is used to direct the interviews and keep them on a path consistent with the purpose of the study[53]. The format is semi-structured, with open-ended questions followed by probing questions, if indicated. Patients are asked how they felt about the treatment they received, whether it met their expectations, and what they liked and disliked about treatment. They are also asked to identify factors considered when determining their satisfaction with care. Providers are interviewed when the study is completed. These interviews explore the clinicians' experiences working with other providers in their respective mono- and multidisciplinary clinical care teams, as well as the perceived usefulness of the care pathways.

Permission is sought to audio-record the interviews, and patients are assured confidentiality, allowing them to speak freely in response to the questions[52]. All interviews are transcribed for analyses. To ensure consistency over the course of the study, audio-taped interviews are monitored for standardized interview techniques and 10% of interview transcripts are randomly sampled and compared to recorded interviews for accuracy.

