## Data Analysis

### Treatment Effectiveness

Power was calculated to detect an 8 to 9 percentage point difference between groups in the primary outcome measure of patient self-reported pain after 12 weeks and one year. A sample size of 100 patients per group provides 80% power assuming an alpha level of .05. This allows for a 15% loss to follow up.

Mixed-Model analysis of covariance (ANCOVA) will be used to test for differences between groups in patient-rated primary and secondary outcomes in both the short- (12 weeks) and long-term (52 weeks). Baseline values will be used as covariates when appropriate; intention-to-treat analysis will be used[60]. A sensitivity analysis will be performed, including patient expectations as a covariate to assess its influence on study results.

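### The between-arm chi-square on interview responses counts responses, not patients, so its p-values and intervals are not valid as written

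*Protocol article*

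**What the plan says.** The between-arm analysis of the interviews is in the protocol article under Data Analysis, Qualitative Analysis: "The frequency of responses in the thematic categories will be cross-tabulated with treatment group assignment and compared for between-group differences using Chi-square analysis". The next sentence reads: "95% confidence intervals will be calculated for these differences". No allowance for dependence within a patient is mentioned for either.

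The same section describes what is coded: "Subsequent transcripts will be independently reviewed to identify and code text segments and to assess the inter-rater reliability of text coding". The unit of coding is therefore a piece of text, not a patient.

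The source of the text is described under Qualitative measures. There is one interview per patient: "Qualitative interviews are conducted with patients individually at the end of the 12-week treatment period". On its form: "The format is semi-structured, with open-ended questions followed by probing questions, if indicated". Patients are asked for likes and dislikes, and also: "They are also asked to identify factors considered when determining their satisfaction with care". Several answers from one person are invited by design.

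**The concern.** Pearson's chi-square assumes that each count in the table is an independent observation. Patients were randomized and interviewed one by one, so the patient is the independent unit. If the table counts responses, a patient who gives three responses enters three times. The table total then exceeds the number of independent units, and the test uses the wrong variance. The same holds for an interval calculated from those counts.

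At stake is the reliability of statements that a theme was raised more often in one arm than in the other. This is the only inferential comparison the article specifies for patients' perceptions of care. A talkative minority could produce an apparent difference or, under another pattern of answering, a real difference could be missed.

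**Working it through.** **No figure to reproduce.** The article gives no sample size, response rate or error rate for this comparison. Its only power statement ("A sample size of 100 patients per group provides 80% power assuming an alpha level of .05") concerns pain. The check is therefore how far the actual size of a nominal 5% test moves under stated assumptions.

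**Inputs**
- From the article: 100 patients per group, 1:1 allocation, 15% loss to follow-up. The loss allowance was planned for the pain outcome. Applying it to the interviews is an assumption and gives 100 x 0.85 = 85 per group in the simulations.
- Assumed: m, the number of coded responses per patient, equal for all patients (2, 3 or 5); and rho, the within-patient correlation of the indicators that a response falls in a given category (0.1 to 0.5). The article gives neither.

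**Step 1. Positive correlation, one category against the rest (1 df).**
Design effect DE = 1 + (m - 1) x rho. Actual size = 2 x [1 - Phi(1.96 / sqrt(DE))]. A correct interval would be wider by sqrt(DE).

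| m | rho | DE | Actual size | Width factor |
|---|---|---|---|---|
| 1 | any | 1.0 | 5.0% | 1.00 |
| 2 | 0.1 | 1.1 | 6.2% | 1.05 |
| 2 | 0.3 | 1.3 | 8.6% | 1.14 |
| 2 | 0.5 | 1.5 | 11.0% | 1.22 |
| 3 | 0.1 | 1.2 | 7.4% | 1.10 |
| 3 | 0.3 | 1.6 | 12.1% | 1.26 |
| 3 | 0.5 | 2.0 | 16.6% | 1.41 |
| 5 | 0.1 | 1.4 | 9.8% | 1.18 |
| 5 | 0.3 | 2.2 | 18.6% | 1.48 |
| 5 | 0.5 | 3.0 | 25.8% | 1.73 |

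Worked line: for m = 3 and rho = 0.3, DE = 1 + 2 x 0.3 = 1.6; 1.96 / sqrt(1.6) = 1.55; the two-sided tail area is 12.1%.

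**Step 2. Positive correlation, all categories in one table.**
A 2 x 5 table was simulated under no difference between arms: 85 patients per group, five equally common categories (assumed), 4,000 runs. The size was 7.0% (m = 2, rho = 0.1), 12.3% (m = 2, rho = 0.3), 9.6% (m = 3, rho = 0.1) and 20.8% (m = 3, rho = 0.3). With more degrees of freedom, the same design effect does more harm.

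**Step 3. Distinct themes, pooled in one table.**
Suppose each patient names m different themes out of five, each counted once, and all go into one 2 x 5 table. Responses within a patient now repel each other: the correlation is -(1/5)^2 / [(1/5)(4/5)] = -0.25, so DE = 1 - 0.25 = 0.75 for m = 2 and 1 - 0.50 = 0.50 for m = 3. The simulated size was 1.2% and 0.05%. The test is still wrong, but now conservative.

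**Step 4. Patient as the unit.**
Each theme was scored yes or no once per patient and tested in its own 2x2 table (85 per group, theme prevalence 30% assumed, 20,000 runs). The simulated size was 4.8%, which agrees with the nominal 5% within simulation error.

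**The case against.** The strongest reply is that the article never says a theme is counted more than once per patient. A response could mean a patient's answer to a question, with each patient classed as raising a theme or not. On that reading Step 4 applies and the chi-square is sound. This stands as a possible reading, and it is why the point is about wording rather than a proven error in execution. But the words used name responses, the coding is by text segment, and nothing limits a patient to one count per theme.

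A reader might also infer that the p-values are necessarily too small and the intervals too narrow. The document does not support that. It invites several different answers per patient, and Step 3 shows that pooling these makes the test conservative. The values of m and rho are not in the article either, so no single inflation figure can be claimed.

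A second tempting inference concerns the evolving code book: "Investigators will meet after each set of twenty interviews to revise the code book and add new codes as necessary". One might conclude that early transcripts are never re-coded, and that a code added after 100 of 200 interviews has its count halved. The halving holds only if the theme was equally common but uncoded in the first hundred. The article is silent on re-coding, which a condensed article can leave to a coding manual. It does have investigators check the summaries against the source text. Under 1:1 blocked allocation, any undercount should affect both arms about equally. This is not a separate error that the document shows.

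Finally, it would overstate matters to say that all conclusions about perceptions depend on this table. The same section also relies on themes, representative quotations, matrices and consensus.

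**Conclusion.** The point holds in conditional form. If responses are counted as the text says, the observations are not independent and the chi-square p-values and intervals are not valid. With positive within-patient correlation of 0.1 to 0.5, a nominal 5% test has an actual size of about 6% to 11% at two responses per patient and 7% to 17% at three. With several distinct themes per patient pooled in one five-category table, the size falls to about 1% or below. These figures rest on assumed response counts and correlations, equal counts per patient and, in the simulations, 85 interviewed patients per group. If each theme is in fact scored once per patient in its own table, there is no problem and only the wording needs correcting. Severity is low, because nothing outside the qualitative between-group comparison is affected.

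**What to change.** State that the patient is the unit of the between-arm comparison. Score each theme as mentioned or not mentioned, once per patient. Compare the proportion of patients mentioning it by arm in one 2x2 table per theme, and report the risk difference with a 95% CI. Use Fisher's exact test where counts are small. If the investigators prefer to keep counts of responses, they need a method that allows for clustering within the patient, such as a cluster-adjusted test or a bootstrap that resamples patients.

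The cost is a change of wording and a per-patient summary of codes already held in the database; no new data are needed. The loss is a little information on how often a patient returns to a theme, which can still be described without a test. Applying the final code book to all transcripts before counting is sensible practice and could be stated in the same sentence, at the price of some coder time.

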## Discussion

The design of this randomized clinical trial (RCT), with cost-effectiveness and qualitative studies conducted alongside the RCT is innovative in several ways.

First, it uses flexible clinical care pathways, which allow for provider and patient choice within the context of study protocols. The ability of the clinician to assess change in the patient's self-selected symptoms mimics real-world care, while also valuing the provider's clinical experience. It also forces, in the multidisciplinary treatment arm, discussion across disciplines; when patients don't meet benchmarks, their case is returned to the care team for review and possibly a change in treatment plan. It has been suggested that combining modalities could have a synergistic effect that might lead to greater improvements;[67] this trial encourages the combination of CAM and conventional treatment. Finally, allowing patients to express their treatment plan preference may increase positive treatment effects. Although this study cannot examine preference alone, patients' qualitative experiences will be captured, which can lead to greater understanding of how preference may influence treatment outcomes.

Second, the multidisciplinary intervention is a non-hierarchical model where consensus is reached among the conventional medicine and CAM team members when formulating treatment plans. The advanced level of integration of the multidisciplinary team, where disparate practitioners reach decisions and consensus as a group, will inform future endeavors by modeling one possible method of practice.

Finally, this study applies the best available evidence for both conventional medicine and CAM to meet the needs of individual LBP patients. Individualizing care has the potential to maximize outcomes in non-specific low back pain when multiple efficacious treatments by themselves have modest effects when applied to the group overall. This study may add to our understanding of the biopsychosocial model of low back pain and whether it could be translated into a useful profile of each patient to guide care.

The study is anticipated to be completed in 2010, at which time results will be made available.
